#### Assignment of interventions: Blinding

*Who will be blinded*. Research team members, who apply the ear clips and set stimulation parameters, are not blinded to treatment arm. The participant, the medical team who dictates all management decisions for the patient’s subarachnoid hemorrhage, and outcomes assessors (those who assign modified Rankin scores at admission, discharge, and at each outpatient follow-up appointment) are blinded to treatment arm. Stimulation parameters are sub-sensory, meaning there is no perceived sensation in the setting of stimulation.

*Procedure for unblinding if needed*. There are no proposed circumstances in which unblinding will be performed. If there are concerns regarding adverse events from the intervention then treatment sessions can be ended prematurely, without revealing treatment group.

#### Data collection and management

*Plans for assessment and collection of outcomes*. Collected data regarding patient clinical presentation, hospital events, clinical outcomes, results from imaging studies, and serial laboratory data will be collected and stored via REDCap. The web-based interface is designed specifically for clinical trials and prospective observational studies. REDCap and the electronic health record will be used for all data collection.

*Plans to promote participant retention and complete follow-up*. The intervention is only administered during the patient’s hospital stay, so there are no foreseeable barriers to retaining participants during the intervention period. Required blood collection is drawn from an indwelling line when available, or is collected at the same time as a patient’s otherwise collected blood samples if venipuncture is required to minimize additional needle sticks that may dissuade ongoing participation during the hospital stay. All primary endpoints are collected during the hospital stay, with no foreseeable barriers to obtaining this clinical information. Following discharge, the patient is not required to make additional visits. Some exploratory outcomes are tracked following discharged but will not be part of the primary analysis. Not mandating additional study visits minimizes the burden on enrolled patients, and further encourages retention in the study long-term.

*Data management*. Data entry input into RedCap undergoes second user validation to confirm data quality. All analysis of continuous variables includes identification of outliers to assess for errors in data collection or reporting.

*Confidentiality*. During this study, medical history (medical diagnoses, surgical history, current medications), information about a patient’s clinical course during hospitalization (medications or procedures performed, radiology exams obtained, and physical exam findings and functional assessments), as well as laboratory data (samples from blood and cerebrospinal fluid) will be assessed. All of the materials collected are for research purposes only, and data will be kept in strict confidence. No identifiable information will be given to anyone without permission from the subject. The consent form includes the informed consent statement required by Washington University for studies involving PHI. Confidentiality will be ensured by use of unique identification codes. Data will be de-identified and stored with an assigned ID number. Data access will be limited to study staff. Data and records will be kept locked and secured, with any computer data password protected. No reference to any individual participant will appear in reports, presentations, or publications that may arise from the study.

The database will be secured with password protection. The informatics manager will receive only coded information that is entered into the database under those identification numbers. Electronic communication with outside collaborators will involve only unidentifiable information. Additionally, all traceable data from copied medical records will also be removed.

*Plans for collection*, *laboratory evaluation and storage of biological specimens for genetic or molecular analysis in this trial/future use*. While blood and cerebrospinal fluid samples are collected in this study, there are no current plans for genetic analysis. In this trial, analysis of biological samples is limited to evaluation of inflammatory cytokines as described previously, which are stored labeled only with the deidentified study ID number. However, the informed consent does include an additional request for approval to allow data and collected biological specimens to be used in future research.

#### Statistical methods

*Statistical methods for primary and secondary outcomes*. The primary outcome of Aim 1 is quantified continuous measures of the plasma and CSF TNF-α collected at two time points, baseline (before treatment) and day 13 after treatment. The taVNS impact on SAH inflammatory markers will be examined via a linear mixed model, where time (i.e., 0- and 13-days post-treatment), treatment (i.e., taVNS vs. Sham), and time-treatment interaction are the fixed effects, and the dependency of measurements clustered within each individual patient will be accounted for via the random effects. Group differences regarding the local and systemic inflammatory cytokines reduction from baseline to day 13 post-treatment will be examined through the interaction of time and treatment effects. Model assumptions will be inspected, and remedy will be applied if necessary. Secondary outcomes involve exploratory analyses of the remainder of the inflammatory markers collected from plasma and CSF.

The primary outcome of Aim 2 is the highest severity of vasospasm (binary, moderate/severe vs. non moderate/severe) as assessed by measurements performed by a Neurointerventionalist. A mixed effect logistic regression model will be used to examine the taVNS and Sham group difference regarding the severity of vasospasm. A generalized estimating equation (GEE) approach will be used to estimate the model parameters assuming a compound symmetry covariance structure, given there might be a possible unknown correlation between observed outcomes within the same patient. For other secondary clinical metrics related to vasospasm, to detect treatment group differences, based upon the distribution of data, independent t-tests or Wilcoxon–Mann–Whitney tests will be performed for continuous variables, and Chi-square tests or Fisher exact tests will be performed for categorical variables.

The primary outcome of Aim 3 is binary (i.e., shunt vs. non-shunt) and the secondary outcome of Aim 3 is continuous (i.e., the duration of external ventricular drainage). To detect the treatment group difference, a 2x2 contingency table and Chi-square test will be used for the binary outcome, and an independent t-test will be used for the continuous outcome.

*Interim analyses*. The principal investigators or study staff will review all data collection forms on an ongoing basis for data completeness and accuracy as well as protocol compliance. See Table 1 for data type, frequency of review, and reviewer. A statement reflecting the results of the ongoing data review will also be incorporated into the Annual Report for the Independent Monitor.

**Table 1 pone.0301154.t001:** Frequency and personnel for trial conduct auditing.

Data type	Frequency of review	Reviewer
Subject accrual (including compliance with protocol enrollment criteria)	Quarterly	PI, Independent Monitor
Status of all enrolled subjects, as of date of reporting	Quarterly	PI, Independent Monitor
Clinical Endpoints/Outcomes Data	Quarterly	PI, Independent Monitor
Laboratory Endpoints	Quarterly	PI, Independent Monitor
AEs and rates	Quarterly	PI, Independent Monitor
SAEs	Per occurrence	PI, Independent Monitor, NIH

The Independent Monitor is appointed to monitor the conduct of the study and subject safety by periodically reviewing data from the study. The Independent Monitor will oversee the overall safety of the study subjects by protecting them from avoidable harm. The Independent Monitor will review adverse events and other relevant study data and will make recommendations regarding continuation of the study to the Principal Investigators. The Principal Investigators will agree to follow the recommendation of the Independent Monitor. This may include termination or suspension of enrollment of the study at any time if it becomes necessary to protect the best interests of the study subjects as advised by the Independent Monitor. If suspicion of an unacceptable risk to participants arises during the conduct of the study, the Independent Monitor, Principal Investigators, institutional review board (IRB), and/or NIH may choose to suspend enrollment until the risk is assessed and a determination is made about the risk. If unacceptable risk is confirmed, the study will be terminated. Decisions to suspend or terminate will be communicated to the IRB. At the time of enrollment suspension or termination a determination will be made about safety follow up assessments required for previously enrolled subjects. The Principal Investigators will notify enrolled subjects, as appropriate, of new information and/or safety follow up assessments as required. Circumstances that may warrant termination or suspension include, but are not limited to: 1) Determination of unexpected, significant, or unacceptable risk to participants, 2) Demonstration of efficacy that would warrant stopping, 3) Insufficient compliance to protocol requirements, 4) Data that are not sufficiently complete and/or evaluable, 5) Determination that the primary endpoint has been met, 6) Determination of futility. The study may resume once concerns about safety, protocol compliance, and data quality are addressed, and satisfy the IRB, Independent Monitor, and NIH.

*Methods for additional analyses (e*.*g*. *subgroup analyses)*. To evaluate for effect of grade of hemorrhage (high grade with a Hunt and Hess Score ≥3, versus low grade), the interaction between assigned treatment and the subgroup factor in a linear model will be tested (significance level of P<0.017). The model will include a main effect for treatment, subgroup factor, and an interaction between subgroup and treatment. Secondary outcomes will also be assessed in similar models.

*Methods in analysis to handle protocol non-adherence and any statistical methods to handle missing data*. High levels of missing data for the outcomes of interest are not expected because these are readily available, documented in medical records as part of the standard of medical care for SAH, and are ascertained during the patient’s primary hospital admission. Should there be high rates of participant attrition in the trial, baseline characteristics and available information on the hospital course will be reviewed and compared to participants who do not withdraw from participation to assess for any differences in those who withdraw and those who do not.

*Plans to give access to the full protocol*, *participant level-data and statistical code*. A dataset with group-level, de-identified clinical data and participant-level de-identified laboratory data in accordance with the Health Insurance Portability and Accountability Act (HIPAA), as well as statistical code used for analyses and will be made available upon reasonable request. The team will comply with the clinical trial information dissemination expectations of the NIH policy and FDA/DHHS Final Rule to register and submit summary results at ClinicalTrials.gov. Consistent with the terms and conditions of NIH funding, we will ensure the submission and updating of registration and results information for this clinical trial in the timeframes established by the Final Rule.

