#### Sample size

Goal enrollment for the pilot NAVSaH trial is 50 patients, based on power calculations to detect significant differences in inflammatory cytokines, radiographic vasospasm, and chronic hydrocephalus.

Under a 2-by-2 repeated measures design consisting of two groups of patients, each measured at two time points, our goal is to compare the change across time in the taVNS group to the change across time in the Sham group. Based upon previous work from Koopman et al. [67], we assume our study will observe 1.1 standardized inflammatory cytokines mean change difference between the two groups. Using a two-sided, two-sample t-test, assuming both time points have equal variance and there is a weak correlation (i.e., 0.15) between measurement pairs, a sample size of 25 in each group achieves at least 80% power to detect a standardized difference of 1.1 in mean changes, with a significance level (alpha) of 0.05 [68].

Based upon our preliminary data, we assume this study will observe 25% and 55% severe vasospasm in the taVNS and Sham groups, respectively. Under a design with 2 repeated measurements (i.e., 2 raters), assuming a compound symmetry covariance structure with a Rho of 0.2, at a significance level (alpha) of 0.05, a sample size of 25 in each group achieves at least 80% power when the null proportion is 0.55, and the alternative proportion is 0.25 [69–71].

As previously described, LV et al. [8] studied the relationship between cytokine levels and clinical endpoints in SAH, including hydrocephalus. From their outcomes, we predict a needed enrollment of approximately 50 to detect these endpoints. From our own preliminary data, with an incidence of chronic hydrocephalus 0% in treated patients and 28.6% in control (despite grade of hemorrhage), alpha = 0.05 and power = 0.80, the projected sample size to capture that change is approximately 44 patients.

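### The primary TNF-α test, a time-by-treatment interaction with free baseline means, is valid and adequately powered but less precise than adjusting for baseline: about 74% more variance at the plan's own correlation of 0.15

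*Protocol article*

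**What the plan says.** Under Statistical methods, the primary outcome of Aim 1 is plasma and CSF TNF-α "collected at two time points, baseline (before treatment) and day 13 after treatment". In the model, time, treatment and "time-treatment interaction are the fixed effects", with patient random effects. The arms are compared on "reduction from baseline to day 13 post-treatment will be examined through the interaction of time and treatment effects". The Outcomes section repeats that the interaction is the primary comparison.

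The Sample size section powers the same contrast: "our goal is to compare the change across time in the taVNS group to the change across time in the Sham group". It uses a two-sided two-sample t-test with 25 patients per group, "assuming both time points have equal variance", and supposes that "there is a weak correlation (i.e., 0.15) between measurement pairs". The sample is said to give at least 80% power "to detect a standardized difference of 1.1 in mean changes", "with a significance level (alpha) of 0.05".

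No section uses baseline TNF-α as a covariate or sets the baseline means equal across arms. The choice of test is fixed in this text, so it is not a detail left to an analysis plan that is not shown.

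**The concern.** With two time points and a separate baseline mean for each arm, the interaction is the difference between arms in mean change. Subtracting baseline helps only when baseline predicts day 13 well. At a correlation of 0.15 it predicts little, and the subtraction mostly adds the noise of a second measurement. Randomisation makes the true baseline means equal, and the planned model does not use that fact.

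At stake is precision on the trial's primary biological endpoint, in a trial of 50 patients. The sample size leaves little room on one reading of the effect size, and day-13 samples may be incomplete: the Outcomes section has blood drawn only during the hospital stay, and CSF only while an external ventricular drain is in place.

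**Working it through.** **Inputs (Sample size section):** 25 per group; equal variance σ² at both times; correlation ρ = 0.15; effect 1.1; two-sided alpha 0.05.

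**1. The plan's own figure.**
- Variance of change = 2(1 − ρ)σ² = 2 × 0.85σ² = 1.70σ², so its SD is 1.304σ.
- If 1.1 is in single-measurement SDs, noncentral-t power with 48 df is 83.2%, and 24 per group are needed for 80%.
- If 1.1 is in SDs of change, power is 96.8%.
- Both readings satisfy the stated power of at least 80%, so the figure is reproduced.

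**2. The interaction is the change score.** In six simulated data sets with 25 complete pairs per group and ρ = 0.15, the mixed-model interaction estimate equalled the difference in mean change to numerical precision. The standard errors agreed except where the random-intercept variance was estimated at or near zero.

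**3. Variance under each analysis (complete pairs).**
- Change score: 1.70σ².
- Day 13 alone, ignoring baseline: 1.00σ².
- Baseline-adjusted: (1 − ρ²)σ² = (1 − 0.0225)σ² = 0.9775σ².
- Ratio of change score to adjusted: 2(1 − ρ)/(1 − ρ²) = 2/(1 + ρ) = 2/1.15 = 1.739.

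The change score is worse than ignoring baseline whenever 2(1 − ρ) > 1, that is, for any ρ below 0.5. In 40,000 simulated trials of 25 per group the ratio was 1.715, because the adjusted analysis must estimate a slope.

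| ρ | Ratio 2/(1 + ρ) | Excess variance |
|---|---|---|
| 0.15 | 1.74 | 74% |
| 0.3 | 1.54 | 54% |
| 0.5 | 1.33 | 33% |
| 0.7 | 1.18 | 18% |

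**4. Power with 25 complete pairs per group, ρ = 0.15** (noncentral t; 48 df for change, 47 df adjusted).

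| Reading of 1.1 | Change score | Baseline-adjusted |
|---|---|---|
| Single-measurement SDs | 83.2% | 97.1% |
| SDs of change (1.1 × 1.304σ = 1.434σ) | 96.8% | 99.9% |

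On the first reading, 80% power needs 24 complete pairs per group for the change score and 14 with adjustment.

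**5. Fewer day-13 samples.** The article gives no expected number, so 15 and 12 per arm are illustrations. Let m be the number of day-13 samples per arm. Two patterns bound the planned test:
- The other patients also lack a baseline. The variance per arm is 1.70σ²/m.
- All 25 baselines per arm are kept and day 13 is missing at random. The mixed model uses those baselines, and the variance per arm is [(1 − ρ²)/m + (1 − ρ)²/25]σ². For m = 15 this is 0.0652 + 0.0289 = 0.0941, which is 1.44 times the adjusted 0.0652. For m = 12 it is 0.0815 + 0.0289 = 0.1104, which is 1.35 times the adjusted 0.0815.

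Power, with 1.1 in single-measurement SDs:

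| Day-13 samples per arm | Planned test, no other baselines | Planned test, all 25 baselines | Baseline-adjusted |
|---|---|---|---|
| 15 | 61% | 69% | 84% |
| 12 | 51% | 61% | 74% |

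**The case against.** The strongest reply is that nothing here is wrong. The question, the power calculation and the test all concern change against change; they agree with one another, and the stated power is correct. That stands. A reader might infer from the 74% that the test is invalid or the trial underpowered as planned, and the document supports neither inference.

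Other limits also stand:
- The correlation of 0.15 is a planning assumption, not an observed TNF-α correlation, so 74% is not a known loss. The table over ρ shows how the excess shrinks.
- If 1.1 is in SDs of change, the power gain at full sample size is negligible (97% to 99.9%).
- A reader might infer that the relative loss is greatest for CSF, where fewest pairs are likely. This does not follow. If drains come out before day 13 and baselines are kept, the excess variance falls as day-13 samples are lost (44% at 15, 35% at 12). It stays at 74% only if those patients have no baseline either, as patients who were never drained would not.
- Chance baseline imbalance, which simple randomisation of 50 patients does not limit, might be read as bias. Averaged over randomisations it is not. It is the same imprecision seen after a particular draw.
- Baseline adjustment is not superior at every correlation in small samples. With ρ very close to 1, estimating the slope can cost slightly more than it gains.

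None of this removes the point that a more precise analysis of data already being collected is available at almost no cost.

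**Conclusion.** The point holds as one of efficiency. The planned interaction test is valid and meets its stated power, but with complete pairs, equal variances and ρ = 0.15 its variance is about 74% larger than with baseline adjustment (about 72% at 25 per group), and larger than if baseline were ignored. In power this is 83% against 97%, or 97% against 99.9%, depending on the units of 1.1, which the article does not settle. With incomplete day-13 sampling the gain can be material on the first reading (61% or 69% against 84% with 15 samples per arm), but its size depends on the missing pattern. The complete-pair ratios rest on the plan's equal variances; the all-baselines figures also assume day 13 is missing at random.

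**What to change.** State that the primary TNF-α comparison, for plasma and for CSF, is the day-13 treatment difference adjusted for baseline TNF-α. Preferably keep the mixed model, constrain the baseline means to be equal across arms (drop the treatment main effect and test the time-by-treatment term), and use an unstructured covariance. This retains patients with one sample missing. ANCOVA of day 13 on treatment and baseline serves for complete pairs, but the two are not interchangeable when samples are missing, because ANCOVA drops those patients. The Sample size section should also say in which SD units the 1.1 is expressed.

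The enrolment target need not change. The cost is a sentence in the analysis section and the estimation of one slope, which is negligible unless ρ is very close to 1. The change should be made before any unblinded analysis.

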### Oversight and monitoring

*Composition of the coordinating center and trial steering committee*. This is a single-center study. There are no other sites participating in the study and there is no need for a separate administrative or data coordinating center. This center’s study team will recruit and enroll study participants under the delegation and supervision of the site’s Principal Investigators from our Washington University School of Medicine Barnes Jewish Hospital’s patient population.

The research team is comprised of senior investigators in the Departments of Neurosurgery, Biomedical Engineering, and Neurology, who have expertise in the fields of subarachnoid hemorrhage, neuroinflammation, electrical stimulation, and clinical trials. The team’s responsibilities include assessment of trial enrollment progress, overall supervision of the trial, and periodic review of the progress of the study to review safety data.

The lead principal investigator is responsible for overseeing the collection and analysis of data, as well as supervising additional team members who are responsible for identifying potential participants, consenting and enrolling patients, and delivering all treatment sessions.

Communication is facilitated with weekly 1-hour laboratory group meetings where working issues are reviewed, and any difficulties with the technology, data acquisition, transfer, and analysis are addressed. In addition, every week, there is a 2-hour scientific review of the project work. The principal investigators and research team attend these meetings routinely. In addition, an administrative review meeting for budget and grant administration will be undertaken every 3–4 months.

*Composition of the data monitoring committee*, *its role and reporting structure*. An Independent Monitor who is a Neurosurgical faculty at Washington University who is not associated with this research project and thus works independently of the PI, research team, and funding agencies has been assigned to provide additional periodic review of subject enrollment, clinical endpoints/outcomes, laboratory endpoints, and all reported adverse events. This individual is not a part of the key personnel involved in the study, and is qualified to review the patient safety data generated by this study because of their expertise in the areas of Neurosurgery and Neurology.

*Adverse event reporting and harms*. An adverse event (AE) is any untoward medical occurrence in a subject during participation in the clinical study or with use of the experimental agent being studied. An adverse finding can include a sign, symptom, abnormal assessment (laboratory test value, vital signs, electrocardiogram finding, etc.), or any combination of these.

A serious adverse event (SAE) is any adverse event that results in one or more of the following outcomes:

DeathA life-threatening eventInpatient hospitalization or prolongation of existing hospitalizationA persistent or significant disability/incapacityA congenital anomaly or birth defectAn important medical event based upon appropriate medical judgment

SAEs that are unanticipated, serious, and possibly related to the study intervention will be reported to the Independent Monitor and IRB in accordance with requirements.

Unexpected fatal or life-threatening AEs related to the intervention will be reported to the NIH Program Officer within 7 days. Other serious and unexpected AEs related to the intervention will be reported to the NIH Program Officer within 15 days.Anticipated or unrelated SAEs will be handled in a less urgent manner but will be reported to the Independent Monitor, IRB, NIH, and other oversight organizations in accordance with their requirements. In the annual AE summary, the Independent Monitor Report will state that they have reviewed all AE reports.

*Frequency and plans for auditing trial conduct*. Table 1.

*Plans for communicating important protocol amendments to relevant parties (e*.*g*. *trial participants*, *ethical committees)*. All protocol amendments will be reviewed by the study investigators, Principal Investigators, and the Washington University IRB committee. This includes main protocol amendments, revisions of any consent paperwork, and continuing reviews. Any protocol amendments that impact enrolled patients will be communicated to patients as deemed appropriate per review and recommendations by the IRB and Independent Monitor.

